The prevalence of NP carriage of VT pneumococci from Jan–Sept 2015 was 17% and fell to 15% in Oct–Dec 2015 (author’s own data). Assuming VT prevalence of 13% in the 3 + 0 group at the beginning of the trial, a 15% loss of impact translates to prevalence in the 1+ 1 group of (1 − [0.72 − (0.72 × 0.15)]) × 47% = 18.3%. We used changes in VT prevalence to inform the non-inferiority margin because reductions in VT carriage following the introduction of PCV can predict the impact of PCV on IPD and because carriage prevalence is proportional to the rate of pneumococcal transmission in the population [42].

For the secondary endpoints of community pneumococcal carriage, the non-inferiority margin of a ≤15% loss of impact in the 1+ 1 compared to the 3+ 0 schedule clusters, will be used as described above. The same VT prevalence will be assumed within the community.

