### Sample size {14}

Sample size calculations were based on the primary outcome of NP carriage of VT pneumococci in children aged 2 weeks–59 months with clinical pneumonia. The primary outcome will be measured in random samples of participants in each of the 68 clusters (if a minimum of 60 participants were sampled in each cluster there would be 1980 in each arm and 3690 in total). Using Basse data from 2015, we assumed that the prevalence of VT carriage to be 13% in both the 3 + 0 and 1 + 1 arms. Based on the non-inferiority assumptions presented in the previous section, the 1 + 1 schedule will be considered non-inferior if the upper limit of the one-sided 95% confidence interval for the prevalence ratio is ≤1.38 (0.18/0.13 = 1.38). Using Basse data, we estimated the intra-class correlation (ICC) to be 0.01–0.02. We calculated study power using the methods of Farrington et al. [43] and Donner et al. [44]. Using the more conservative value for ICC of 0.02, a minimum number measured for the endpoint per cluster of 60, 33, and 35 clusters per arm (with design effect of 2.18) and alpha=0.05, a sample size of 1980 per arm will provide 93% power to test the non-inferiority of the 1 + 1 schedule.

To increase confidence in the power of the study we simulated trial data using 2015 data from the BHDSS based on cluster-wise VT carriage in children with pneumonia. The simulated data were designed to be similar to the villages included in this trial with respect to the mean carriage prevalence, as well as the variability in prevalence across clusters. Using 1000 simulated populations, each consisting of 68 clusters of 60 individuals, baseline prevalence of 10% and a largest acceptable increase of 4%, i.e. from 10 to 14%, study power was ≥85% in most scenarios.

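### The stated 93% power is not that of the prevalence-ratio test the protocol defines, which has about 84–85% power at ICC 0.02; the stated arm sizes and total are also wrong

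*Protocol article*

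**What the plan says.** All references are to the protocol article.

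- **Assumed truth.** Under Sample size {14}: "we assumed that the prevalence of VT carriage to be 13% in both the 3 + 0 and 1 + 1 arms".
- **Criterion.** The same section uses the "upper limit of the one-sided 95% confidence interval" and sets the limit on the ratio: "confidence interval for the prevalence ratio is ≤1.38 (0.18/0.13 = 1.38". Statistical methods {20a} repeats the 1.38 limit for a prevalence ratio estimated by log-link GEE.
- **Clustering.** "Using the more conservative value for ICC of 0.02", with "60, 33, and 35 clusters per arm (with design effect of 2.18) and alpha=0.05".
- **Result.** "a sample size of 1980 per arm will provide 93% power to test the non-inferiority of the 1 + 1 schedule". The Farrington and Donner methods are cited, but the scale of the power calculation (difference or ratio) is not given.
- **Sizes.** At 60 per cluster, "there would be 1980 in each arm and 3690 in total".
- **Source of the margin.** The section Non-inferiority margin derives the limiting prevalence as "1 − [0.72 − (0.72 × 0.15)]) × 47% = 18.3" per cent. It chooses a relative metric because an absolute margin may be unreliable if baseline risk changes.
- **Community surveys.** Sample size {14} says they use the same assumptions and methods, with 15% baseline prevalence, ICC 0.02, ratio limit 1.38 and 4080 samples, and claims power above 94%.

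**The concern.** Every input to the power calculation is printed, so the figure can be checked. For a ratio test with limit 1.38 it does not come back: the recomputed power is 8 to 9 points lower. Readers use the stated power to interpret an inconclusive non-inferiority result, and this trial is meant to inform global policy on vaccine schedules. If true power is about 85%, the chance of missing a schedule that really is equivalent is about twice what the text implies. The arm sizes and total printed beside the power also fail simple addition.

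**Working it through.** **Inputs (Sample size {14}).** True prevalence p = 0.13 in both arms; ratio limit 1.38; one-sided alpha 0.05 (z = 1.645); 60 per cluster; ICC 0.02.

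Design effect = 1 + (60 − 1) × 0.02 = 2.18, as printed. Effective size per arm = 1980 / 2.18 = 908.3.

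**Step 1: reproduce 93%.** Treat the margin as an absolute difference, 0.18 − 0.13 = 0.05.

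- SE = √(2 × 0.13 × 0.87 / 908.3) = 0.01578
- Power = Φ(0.05 / 0.01578 − 1.645) = Φ(1.523) = 93.6%

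With the margin as 0.38 × 0.13 = 0.0494, power is 93.1%. The restricted-variance (Farrington-Manning) versions give 93.4% and 92.9%. So 93% follows from the printed inputs on the difference scale.

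**Step 2: power of the test actually defined.** Use the log prevalence ratio.

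- SE(log ratio) = √(2 × (0.87 / 0.13) / 908.3) = 0.1214
- ln 1.38 = 0.3221
- Power = Φ(0.3221 / 0.1214 − 1.645) = Φ(1.008) = 84.3%

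The table gives one-sided power at alpha 0.05 and limit 1.38. The ratio-scale range for 1980 and 2100 allows for either arm being the larger, since the article does not say which arm has 35 clusters.

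| ICC (design effect) | Sizes | Log-ratio Wald | Farrington-Manning ratio |
|---|---|---|---|
| 0.02 (2.18) | 1980 / 1980 | 84.3% | 84.0% |
| 0.02 (2.18) | 1980 / 2100 | 85.2% | 84.8–85.0% |
| 0.01 (1.59) | 1980 / 1980 | 92.8% | 92.5% |
| 0.01 (1.59) | 1980 / 2100 | 93.4% | 93.0–93.2% |

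Two routes therefore lead to about 93%: a 5-point difference at ICC 0.02, or the ratio test at ICC 0.01. The printed design effect of 2.18 is exactly the ICC 0.02 value, so the first route needs no assumption that a printed input was not used.

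**Step 3: sensitivity of the ratio result (1980 per arm, ICC 0.02).**

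- Unrounded limit 18.3 / 13 = 1.41: 87.5–87.9%.
- Limit taken from a two-sided 95% interval (one-sided 0.025), limit 1.38: 75–76%.

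**Step 4: community surveys.** p = 0.15, effective size per arm = 2040 / 2.18 = 935.8.

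- Ratio scale: SE = √(2 × (0.85 / 0.15) / 935.8) = 0.1101; power = Φ(0.3221 / 0.1101 − 1.645) = Φ(1.282) = 90.0% (Farrington-Manning 89.6%).
- Difference scale, margin 0.38 × 0.15 = 0.057: 96.5%. With 5.3 points (18.3% − 13%): 94.1%. With 5 points: 91.7%.

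The claim of more than 94% is met on the difference scale with a margin of 5.3 or 5.7 points, but not on the ratio scale.

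**Step 5: sizes.** 33 × 60 = 1980; 35 × 60 = 2100; total 4080 = 68 × 60. The text gives 1980 in each arm and a total of 3690, yet even 2 × 1980 = 3960. The community-survey paragraph of the same section correctly prints 4080 for 68 clusters of 60.

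**The case against.** The strongest defence is that 93% is obtainable from the printed inputs at the printed ICC, as Step 1 shows. The cited methods do not fix the scale, and the margin is itself displayed through 18% and 13%. The simulation paragraph also describes its margin as an absolute increase, from 10% to 14%. On the difference scale at ICC 0.02 that gives 89%, in line with the reported power of at least 85% in most scenarios. One scale thus fits all the stated powers without changing the ICC. This stands as an account of where the figure probably came from. It does not make 93% the power of the primary analysis: the verdict is defined on the ratio, estimated with a log link, and the margin section gives reasons against an absolute margin.

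A reader might go further and infer that 93% is really the ICC 0.01 result presented under the conservative ICC. The documents do not support that. The difference-scale route explains the figure with the printed design effect, and nothing shows that ICC 0.01 was used. Nor can the simulation be called wrong: it rests on cluster-level 2015 data and several scenarios that are not shown.

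It is also fair that 60 per cluster is a stated minimum, that 1980 is the smaller arm, so using it for both is slightly conservative, and that the total of 3690 (perhaps 3960 with digits transposed) enters no power calculation.

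**Conclusion.** The point holds as a mismatch between the stated power and the specified test. For the prevalence-ratio test with limit 1.38, 13% in both arms, ICC 0.02 and a one-sided 95% limit, power is about 84% with 1980 per arm and about 85% with 1980 and 2100, against 93% stated. The likeliest origin is a calculation on the absolute difference; a different ICC is possible but less likely, and the article does not settle it. The community-survey figure is probably overstated in the same way, at about 90% on the ratio scale if the limit is one-sided, against more than 94%. The arm sizes and the total of 3690 are plain errors.

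These results assume equal clusters of exactly 60, a true ratio of 1 and normal approximations.

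Severity is moderate. Power stays above 80% with the one-sided limit stated in the sample size section. The 75–76% figure would apply only if the 95% intervals in Statistical methods {20a}, where one-sided is not repeated, are two-sided. That is a separate question of wording and not part of the arithmetic error.

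**What to change.** In Sample size {14}:

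1. Restate primary power as about 85% for the prevalence-ratio test at ICC 0.02 and one-sided alpha 0.05, with arms of 1980 and 2100.
2. State the scale and sidedness used for the power calculation. If 93% came from an absolute difference, say so and label it as such. Do not attribute it to ICC 0.01 unless the original calculation shows that.
3. Recompute the community-survey power on the ratio scale (about 90% under the stated assumptions with a one-sided limit).
4. Correct the sizes to 1980 and 2100, total 4080.

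The cost is wording and one recalculation. No participants, clusters or procedures change; a headline figure becomes less favourable.

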### Non-inferiority margin

We determined the non-inferiority margin using the concept of ‘the largest loss of impact of the current treatment that would be clinically acceptable’, an approach recommended by the US FDA [41]. The non-inferiority margin uses a relative metric as the relative effect of the standard schedule is likely to be constant. The introduction of the 3 + 0 schedule has reduced NP VT prevalence in children from 47 to 13%, i.e. a 72% reduction (author’s own data). Baseline risk may change over time, so an absolute value for the non-inferiority margin may not provide a reliable measure of the difference in impact of the two schedules.

Given the important advantages of the 1 + 1 schedule, the non-inferiority margin will be a 15% loss of the impact of the 3 + 0 schedule; this value is supported by empiric survey data. An online survey was sent to 72 individuals involved in pneumococcal vaccine research, policy and clinical care. Valid responses were received from 19 respondents. The survey question presented 10 hypothetical results of VT prevalence in the two trial groups, on a scale of increasing ‘loss of impact’ associated with the 1 + 1 schedule, from a baseline of no loss (i.e. a 0% loss of impact) in the 1 + 1 versus 3 + 0 group, up to a 50% loss of impact. Respondents were asked to consider themselves as decision-makers in their national immunisation programmes requested to consider a change to their national programme from a 3 + 0 to 1+ 1 schedule based on the results of the trial. Respondents selected one option corresponding to the ‘loss of impact’ which would sway their decision against introducing the new 1+ 1 schedule. Using the metric of a percentage loss of impact of the 3 + 0 schedule which would sway decisions against the new schedule the mean value was a 22% loss of impact. The results of the survey support our decision to use a non-inferiority margin that the 1 + 1 schedule be associated with a ≤15% loss of the total impact of the 3 + 0 schedule.

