## Statistical methods

### Statistical methods for primary and secondary outcomes {20a}

Coverage of each schedule during the course of the trial will be reported at the end of each of the four annual periods, as the proportion of surviving, resident children, who have completed the respective schedules at the ages of 12 and 18 months. Coverage calculations will be classified as receiving the respective schedules in a timely (completed before age 7 months [3 + 0] or 13 months [1 + 1]) or delayed fashion. Cross-over between groups will be defined as (a) change of residential location from a 1 + 1 to 3 + 0 cluster, and vice versa, for a period of 4 or more months and (b) receipt of the third dose of PCV at 8 months of age or greater in a 3 + 0 cluster.

The unit of inference will be the individual child. That is, we wish to estimate whether the risk of VT carriage in a child who lives in a geographic area using a 1 + 1 schedule is not greater than the given threshold when compared to a child in an area receiving the 3 + 0 schedule. The primary outcome will be presented as the proportion (prevalence) of children with clinical pneumonia and NP carriage of VT pneumococci. The contrast between the two groups will be presented as a prevalence ratio (and 95% confidence intervals), with ratios expressed as the prevalence in the 1+ 1 group compared to the prevalence in the 3 + 0 group. To account for cluster-level non-independence, the primary analysis will use generalised estimating equations (GEE) with a log link, binomial family and exchangeable correlation structure. The GEE models will adjust for stratification variables, and age will be included in the model for the endpoint of VT carriage in unimmunised infants aged 6-12 weeks, due to rapid age-related changes in prevalence in the first months of life. Non-inferiority will be established if the upper limit of the confidence interval around the prevalence ratio is ≤1.38.

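### The supporting power simulation uses a rise from 10 to 14% instead of the 1.38 prevalence-ratio limit, so it does not establish the power of the primary test at 10% prevalence

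*Protocol article*

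**What the plan says.** The decision rule is relative. Under Statistical methods for primary and secondary outcomes {20a} the model is "generalised estimating equations (GEE) with a log link, binomial family and exchangeable correlation structure", and the criterion reads: "Non-inferiority will be established if the upper limit of the confidence interval around the prevalence ratio is ≤1.38". Sample size {14} gives the same limit as "the upper limit of the one-sided 95% confidence interval for the prevalence ratio is ≤1.38 (0.18/0.13 = 1.38". The Non-inferiority margin section explains why the scale is relative: "Baseline risk may change over time, so an absolute value for the non-inferiority margin may not provide a reliable measure".

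For the main power calculation the article states that "we assumed that the prevalence of VT carriage to be 13% in both the 3 + 0 and 1 + 1 arms". On clustering it states that "we estimated the intra-class correlation (ICC) to be 0.01–0.02", and then: "Using the more conservative value for ICC of 0.02, a minimum number measured for the endpoint per cluster of 60". The power it reports from these inputs is 93%.

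A second paragraph of Sample size {14} adds a simulation meant to strengthen confidence in that power. It uses 1000 simulated populations of 68 clusters of 60, with carriage and between-cluster variability modelled on 2015 BHDSS data. Its setting and result are: "baseline prevalence of 10% and a largest acceptable increase of 4%, i.e. from 10 to 14%, study power was ≥85% in most scenarios".

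**The concern.** The simulation's acceptable increase is worded as a rise in percentage points from a 10% baseline. As a ratio it is 14/10 = 1.40, not 1.38. It also does not follow from the protocol's substantive margin, a 15% loss of impact. With 47% before vaccine and 10% under the standard schedule, a 15% loss gives 10 + 0.15 × 37 = 15.55%, whereas 14% is a loss of 4/37 = 10.8%.

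This is the only power figure in the article for a prevalence below 13%. With a fixed ratio limit, power falls as prevalence falls, because the variance of the log ratio grows with (1 − p)/p. With a fixed difference in points it rises, because p(1 − p) shrinks. A reassurance obtained on one scale therefore need not hold on the other. A committee checking the sample size assumptions could take 85% as the power of the primary test at 10% carriage when the risk of missing true non-inferiority may be nearer one in four.

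**Working it through.** **Inputs.** All are from Sample size {14}: 33 and 35 clusters of 60, so 1980 and 2100 children; ICC 0.01 to 0.02; one-sided 5% level (z = 1.645); ratio limit 1.38. Simulation setting: p = 0.10 in both arms, acceptable prevalence 14%.

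**Formulas.** Design effect DE = 1 + 59 × ICC, which is 1.59, 1.885 and 2.18 at ICC 0.01, 0.015 and 0.02. The last equals the article's value. Let K = 1/1980 + 1/2100 = 0.000981.

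- Ratio limit R: SE = √[((1 − p)/p) × DE × K]; power = Φ(ln R / SE − 1.645).
- Difference d: SE = √[p(1 − p) × DE × K]; power = Φ(d / SE − 1.645).

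**The article's figure first.** With d = 0.04, p = 0.10 and ICC 0.02, SE = √(0.09 × 2.18 × 0.000981) = 0.01387. Then 0.04/0.01387 − 1.645 = 1.238, and power is 89%. At ICC 0.01 it is 96%. An absolute 4-point margin therefore meets the stated 85% over the whole ICC range.

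**The deciding rule.** With R = 1.38, p = 0.10 and ICC 0.02, SE = √(9 × 2.18 × 0.000981) = 0.1387. Then ln 1.38 = 0.3221, 0.3221/0.1387 − 1.645 = 0.676, and power is 75%.

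| Margin at 10% baseline | ICC 0.01 | ICC 0.015 | ICC 0.02 |
|---|---|---|---|
| Ratio 1.38 (trial rule) | 86% | 80% | 75% |
| Ratio 1.40 (14/10) | 88% | 83% | 78% |
| Difference of 4 points | 96% | 93% | 89% |

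A beta-binomial simulation with cluster-robust variance of the log ratio (40,000 trials per ICC, no covariate adjustment) gave 85.8%, 80.0% and 75.0% for the 1.38 rule, in agreement with the formula.

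**Where the 1.38 rule reaches 85%.** The condition is ln 1.38 / SE = 1.645 + 1.036 = 2.681, so SE = 0.1201, DE = 0.01443/(9 × 0.000981) = 1.634, and ICC = 0.634/59 = 0.011. For ratio 1.40 the same steps give about 0.013.

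**If the interval is two-sided.** The analysis section does not repeat that the limit is one-sided. With z = 1.96, power for the 1.38 rule at 10% is Φ(2.321 − 1.96) = 64% at ICC 0.02 and Φ(2.718 − 1.96) = 78% at ICC 0.01.

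**The case against.** - **Rounding.** 1.38 × 10% = 13.8%, which rounds to 14%, and the same section rounds 18.3% to 18%. The simulation may have applied the ratio rule and reported it in whole percentages. This stands as a possibility, and 1.38 against 1.40 is worth only about 3 points of power. But even at 1.40, power is already 83% at ICC 0.015.
- **Test scale and ICC not stated.** A condensed article may leave these to the full protocol, so their absence is not the point here. It does limit the conclusion. The simulation used observed 2015 variability, not ICC 0.02. If that variability corresponded to an ICC near 0.01, the 85% could be correct for the 1.38 rule.
- **ICC varies with prevalence.** If the between-cluster coefficient of variation is constant (an assumption), ICC scales with p/(1 − p). Then 0.02 at 13% becomes 0.02 × (0.1111/0.1494) = 0.015 at 10%, and 0.01 becomes about 0.007. The 1.38 rule then has about 80 to 89% power. This is fair: 75% is the low end of a range.
- **Covariate adjustment.** The primary GEE adjusts for a stratifier chosen for its correlation with carriage, which may absorb some between-cluster variance. The calculation above is unadjusted, and the size of the gain is unknown.
- **Wording.** The article claims the figure only for most scenarios, so it allows for some below 85%.
- **Relevance of 10%.** A reader might infer from the fall since 2009 that 10% is the likeliest outcome and that the simulation conceals it. The documents do not support that. The latest under-5 figures are 15% (2015) and 17% (2017), and at 15% with ICC 0.02 the same formula gives about 90% power under the 1.38 rule.

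What survives is narrower. The margin as written is not the one that decides the trial, and on the ratio scale the stated power is not reached over most of the protocol's own ICC range.

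**Conclusion.** The simulation does not establish the power of the primary test at 10% prevalence. Under the 1.38 rule, power there is about 75% at the planning ICC of 0.02, 80% at 0.015 and 86% at 0.01. At ICC 0.02 this is about 10 points short of the 85% quoted.

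These figures assume equal carriage in the two arms, clusters of exactly 60, a one-sided 95% limit, no gain from covariate adjustment, and a simulated cluster variability within the stated ICC range.

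Two stronger readings are tempting. One is that the 85% is simply false for the primary test. That is not shown, because an ICC near 0.01 would deliver it. The other is that power was calculated on absolute differences throughout. The companion 93% does reproduce at 13%, ICC 0.02 and 1980 per arm with a 5-point difference: Φ(0.05/0.01578 − 1.645) = 94%, against Φ(0.3221/0.1214 − 1.645) = 84% for ratio 1.38. That fits such a reading but does not prove it, since the article does not give the simulation's scale.

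**What to change.** Rerun the simulation with the analysis as specified: log-link GEE, exchangeable correlation, adjusted for the stratification variable, and success defined as an upper limit of the prevalence ratio of at most 1.38. Use prevalences of 10% and 13% and ICCs of 0.01 and 0.02, with the trial's own cluster data. State whether the limit is one-sided.

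Replace the single 85% statement with power by ICC. At 10% the result should be roughly 75 to 86%, but the published numbers should come from the rerun and not from the approximation above. Replace the 10-to-14% margin with the 1.38 rule, or label it as a different margin from the one that decides the trial.

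The cost is a few hours of computing, one rewritten sentence and a less favourable stated figure. No participants are added and trial conduct does not change.

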As opposed to the non-inferiority hypothesis that is specified in year 4 of the study we will specify a superiority hypothesis for the measurement in year 2 of VT prevalence in children with clinical pneumonia. Setting a 5% level of significance and power of 80%, with ICC=0.02 and assuming the prevalence of VT carriage in the control group is 18%, we wish to detect an absolute difference of 8%. That is, the smallest clinically significant difference that we wish to detect is equivalent to 18% versus 26% prevalence in the two groups. Given these parameters, if we measure the endpoint in 20 individuals per cluster, we would need to include 29 clusters in each group, that is, a total of 58 clusters. We will measure the endpoint in 68 clusters.

Study power for the secondary endpoint of VT prevalence in infants aged 6–12 weeks presenting for their first dose of PCV is based on the same assumptions as for the primary endpoint and study power will be similar to that for the primary endpoint.

In the community carriage surveys in years 2 and 4, we will sample 60 residents in each of the 68 clusters. The same assumptions and methods of power calculation as for the primary endpoint were used. We assume ICC=0.02, 15% baseline VT carriage prevalence in both clusters, and a ≤1.38 prevalence ratio derived from the ≤15% NI margin. If the upper bound of the 95% confidence interval of our prevalence ratio comparing the 1 + 1 to the 3+ 0 clusters is ≤1.38, then the alternative schedule will be considered non-inferior. Following these assumptions, the community carriage surveys in years 2 and 4 will have power > 94% if we collect 4080 samples evenly across 68 clusters (i.e. 60 per cluster).

For the interpersonal-contact pattern survey in year 2, 1500 participants from the carriage study will be enrolled. Recruiting 1500 participants will enable us to detect an absolute difference of 1 mean contact per day between age groups, with a 5% significance level, and 90% power. These calculations are based on the work of le Polain de Waroux et al. [45]. The study is not powered to determine non-inferiority for other secondary or safety endpoints.

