### Recruitment {15}

All infants resident in the BHDSS or FWHDSS are eligible for enrolment in the PVS field trial. When infants present to immunisation clinics, trial staff confirm their identity and apply the trial inclusion and exclusion criteria. The mother/guardian of infants who meet the inclusion criteria and do not have exclusion criteria are informed about the nature of the trial as part of the informed consent process. The screening of infants and recruitment of participants is electronically entered in real-time into the trial data management system. A trial sticker is fixed to the child welfare card and the intervention schedule is marked on the child welfare card. Enrolment to receive the 1 + 1 intervention will cease 3 months prior to the close of clinical surveillance at the end of year 4 of the study.

Children aged 2 weeks to 59 months who are resident in the study area are under surveillance for clinical endpoints. Children who present unwell to health facilities in the study area are evaluated for criteria indicating the need for clinical investigation.

The cluster-wise selection of infants aged 6–12 weeks at the first dose of PCV13 for laboratory analysis of NP swabs will include all individuals in clusters with a number of individuals below a threshold number set for statistical efficiency. In clusters with numbers greater than the threshold, selection will follow a random scheme within each cluster. Patients will be randomly sampled within clusters from those born in the trial area, across age, time and space.

For the community surveys of pneumococcal carriage, residents of all ages will be included in the sampling frame. The HDSS will be used to determine cluster, village, and household population sizes and as a reference for the members of a household. Three-level cluster sampling using probability proportional to size will be used to select 2 villages within each of 68 clusters, with three households per village and 10 individuals per household. Ten individuals will be randomly selected from each household following the age-structure ratio 2:2:2:2:1:1 (0–11 months, 12–23 months, 2–5 years, 6–14 years, 15–44 years, 45 years and greater). Individuals not listed as resident within a selected household may be eligible if confirmed by the head of household as resident in the past 4 months.

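### The power above 94% claimed for the community carriage surveys does not match the stated prevalence-ratio rule, which gives about 90% (about 85% at the 13% prevalence used for the margin)

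*Protocol article*

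**What the plan says.** Sample size {14} plans that "we will sample 60 residents in each of the 68 clusters" and sets the inputs: "We assume ICC=0.02, 15% baseline VT carriage prevalence in both clusters, and a ≤1.38 prevalence ratio derived from the ≤15% NI margin". It says that the assumptions and power method of the primary endpoint were reused, and concludes that "the community carriage surveys in years 2 and 4 will have power > 94% if we collect 4080 samples evenly across 68 clusters". The decision rule begins "If the upper bound of the 95% confidence interval of our prevalence ratio" and does not give the sidedness. For the primary endpoint the same section specifies the "upper limit of the one-sided 95% confidence interval for the prevalence ratio is ≤1.38", with alpha 0.05 and design effect 2.18.

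Non-inferiority margin works from 13% in the 3 + 0 group, reaches 18.3% in the 1 + 1 group, and then says of the community endpoint: "The same VT prevalence will be assumed within the community".

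Recruitment {15} describes the survey sample: two villages per cluster, "with three households per village and 10 individuals per household", chosen "following the age-structure ratio 2:2:2:2:1:1" over six age bands.

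**The concern.** The power statement fixes every input that it needs, so it can be checked directly. Under the ratio rule it comes out lower than stated. The prevalence used for it also differs from the one that the margin section assigns to the community.

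The abstract relies on the secondary endpoints to support interpretation of the primary. If the schedules are truly equal, the stated figure implies a chance below 6% that a survey fails to show non-inferiority. On the stated rule that chance is about 10%, and at 13% prevalence about 15%. A reader who trusts the stated figure would read too much into a survey that missed the margin.

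**Working it through.** **Inputs** (Sample size {14} unless noted)
- Sample: 60 × 68 = 4080, about 2040 per arm.
- ICC 0.02, so design effect = 1 + 59 × 0.02 = 2.18 and effective n = 2040 / 2.18 = 936 per arm.
- Prevalence 15% in both arms; ratio limit 1.38; one-sided alpha 0.05, carried over from the primary endpoint.
- Alternative prevalence 13% (Non-inferiority margin).

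**1. Reproducing the stated figures.** Take a two-proportion test of 15% against 0.15 × 1.38 = 20.7%. The standard error is 0.01770 under the null and 0.01765 under the alternative.

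Power = Φ[(0.057 − 1.645 × 0.01770) / 0.01765] = Φ(1.58) = 94.3%.

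For the primary endpoint, with effective n 1980 / 2.18 = 908 and 13% against 18.3%, the same formula gives 92.9%, in line with the stated 93%. This calculation supposes that the arms truly differ by the whole margin and asks how often the difference is detected.

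**2. Power for the stated rule.** Both arms are at 15%, and success means that the upper limit of the ratio is at most 1.38.

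SE(log ratio) = √[2 × 0.85 / (0.15 × 936)] = 0.1101, and ln 1.38 = 0.3221.

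Power = Φ(0.3221 / 0.1101 − 1.645) = Φ(1.282) = 90.0%.

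Other routes agree:
- Farrington-Manning ratio test: 89.6%.
- t reference with 66 degrees of freedom: 89.5%.
- Beta-binomial simulation, 20,000 runs, 34 clusters of 60 per arm: 89.6%.
- 33 and 35 clusters instead of 34 and 34: 90.0%.

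**3. Primary endpoint by the same method.** At 13% and effective n 908, SE = 0.1214. Power = Φ(0.3221 / 0.1214 − 1.645) = Φ(1.008) = 84.3% (Farrington-Manning 84.0%).

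**4. Community survey at 13%.** SE = 0.1196. Power = Φ(0.3221 / 0.1196 − 1.645) = Φ(1.048) = 85.3% (Farrington-Manning 84.9%).

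**5. Two-sided 95% limit at 15%.** Replacing 1.645 by 1.960 gives Φ(0.967) = 83.3% (Farrington-Manning 83.0%).

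**6. Sensitivity only.** With 10 people from each of six households per cluster, the design effect is 1 + 9 × ICC(household) + 50 × ICC(cluster). The protocol gives no household ICC, so the values below are assumptions. Power is one-sided at 15% prevalence, by Farrington-Manning.

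| Cluster ICC | Household ICC (assumed) | Design effect | Power |
|---|---|---|---|
| 0.02 | 0.05 | 2.45 | 86% |
| 0.02 | 0.10 | 2.90 | 81% |
| 0.02 | 0.20 | 3.80 | 71% |
| 0.01 | 0.05 | 1.95 | 92% |
| 0.01 | 0.075 | 2.175 | 90% |

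On age, the last three bands make up (2 + 1 + 1) / 10 = 40% of the sample and are aged 6 years or over. The protocol gives no carriage figure for those ages. At an assumed all-age prevalence of 10% and design effect 2.18, power is about 75%.

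**The case against.** The strongest reply is that the authors made no slip of arithmetic. Their figure reproduces at their own ICC of 0.02, and the formula that gives it also gives the primary 93%. That stands, so a reader should not infer that an ICC near 0.01 was used: 0.01 would also lift the ratio-scale power (to about 96%), but nothing requires it. The protocol does not show its formula, so the two-proportion origin is an inference. A Farrington-Manning test on a fixed difference of 5.7 points gives 96.4%, which is also above 94%. Neither calculation is the ratio rule that the protocol states, so the mismatch remains.

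Three stronger readings are tempting, and the document does not support them.
- **Power is 83% on the stated inputs.** The limit is defined as one-sided for the primary endpoint, and the survey reuses those assumptions. The 83% applies only if the limit is read as two-sided.
- **Household sampling lowers power below 90%, so 90% is a best case.** No household ICC is given. The protocol's range for the cluster ICC is 0.01 to 0.02. At 0.01, a household ICC of up to about 0.075 keeps the design effect within 2.18.
- **The all-age sample has lower prevalence.** This is plausible, but there is no figure for older ages. The under-5 label in the background section is attached to the 47% pre-vaccine value, and the sentence with the later 15% and 17% names no age group.

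It is also fair to say that 90% remains ample for a secondary endpoint.

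**Conclusion.** The stated power above 94% is wrong for the rule to which it is attached. With the protocol's own inputs and a one-sided 95% limit it is about 90%. The cause is a mismatch between the power formula and the ratio criterion, and the same mismatch takes the primary endpoint from 93% to about 84%. The 13% and 15% community prevalences contradict each other, and the choice moves power between about 85% and 90%.

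These figures rest on design effect 2.18, equal prevalence in the two arms and one-sided alpha 0.05. Any further loss from households or age is possible but unquantified in the protocol. The result does not show that the surveys are too small.

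**What to change.** - Recompute and restate the survey power in Sample size {14} for the ratio rule: about 90% at 15%, or about 85% at 13%. Restate the primary endpoint's 93% on the same basis (about 84%).
- Use one community prevalence in Non-inferiority margin and Sample size {14}.
- Say in the survey's decision rule that the 95% limit is one-sided. If a two-sided limit is intended, the figure at 15% is about 83%.
- Add a sensitivity range, labelled as assumption, with design effect 1 + 9 × ICC(household) + 50 × ICC(cluster) and with a lower all-age prevalence.

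The cost is a recalculation and some wording. The stated power becomes less favourable, and no added sampling is needed.
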